# 12. Data collection and management

The trial database/eCRF will be constructed using REDCap software, hosted by the Capital Region. This database complies with Danish data safety legislation.

The data protection act and the data protection regulation is complied with regarding collection and storage of biological material and journal data. No material will be sent abroad.

A research biobank will be established. We will draw blood samples during hospitalizations at admission and after 24 hours. These blood samples will be stored for later analysis (research biobank, approx. 50 ml in total). The purpose of the research biobank is to investigate the effect of oxygen on biomarkers for heart, brain, kidney function and inflammatory reaction. The material is stored for up to 10 years, after which it is destroyed, no later than 1 February 2036. The material is stored pseudo-anonymized. Material will not be sent abroad.

## 11.1 Data sources

Data capture for the eCRF originates from the following sources:

- The screening and randomization log (REDCap survey)
- The eCRF, to be filled out by the site investigator or delegate (Patient electronic chart to CRF)
- Follow-up mailed questionnaires (REDCap surveys)
- Paper consent form or consent from REDcap-survey. Scanned and filed in REDCap AND stored in paper format at the site.
- Biochemistry data pull from LABKA
- Research biobank analyses in Excel, patient trial ID as identifier
- Electronic medical record
- Data from medical devices: Echo-machines, ReDS-machines, and O2MATIC-machines.

## 11.2 Data collection process

In the paper inlay in the sealed box the QR-code (link) to the screening survey in REDcap to fill out at inclusion. In the screening survey, the investigator will enter:

#### Screening

- Fulfilling inclusion/exclusion criteria (yes/no),
- Patient ID (CPR-number),
- running number of the study-medicine kit,
- consent (yes/no) and name from legal guardian
- If the investigator finds the patient eligible for inclusion in the trial (yes/no)

#### Medical history characteristics (at the time of inclusion, T0)

- Age
- Sex
- Height in cm
- Weight in kg (usual weight)
- Previous New York Heart Association (NYHA) classification
- Comorbidity (Heart failure, AMI, arrhythmia, arterial hypertension, previous stroke, previous transitory cerebral ischemia, diabetes type I, diabetes type II, asthma or COPD, renal failure, liver cirrhosis, malignancy, alcohol abuse, drug abuse, HIV, AIDS, previous PCI, previous CABG, previous valve surgery)
- Medications
- Pervious LVEF
- Inclusion / exclusion criteria

#### Data from emergency department (at the time of inclusion, T0)

- Weight in kg (measured in the ED)
- Time of symptom-onset
- Administered study-medicine
- Administered treatment prehospital
- Time of hospital arrival
- Time from hospital arrival to inclusion (calculated)
- Including site
- Blood gas analyses
- Echocardiography if available
- Vital signs at admission and after 1- and 6-hours including blood pressure, heart rate, respiratory rate, and peripheral oxygen saturation.
- Any concomitant therapy
- Routine biochemistry**
- ECG findings (Rhythm; signs of ischemia and QRS configuration: normal, STEMI, NSTEMI, LBBB, RBBB, other)

#### Characteristics Daily During hospitalization

- Echocardiography
- Vital signs
- Any concomitant therapy
- Heart failure medicine
- Biochemistry**
- ECG findings (Rhythm; signs of ischemia and QRS configuration: normal, STEMI, NSTEMI, LBBB, RBBB, other)
- Need for pacing (yes/no)
- Need for Angiography (yes/no)
- Time to PCI (yes/no)
- Time to CABG (yes/no)
- Need for ICU (yes/no)
- Need for vasopressors or inotropes (yes/no)
- Need for mechanical ventilation (yes/no)
- Need for renal replacement
- Chest x-ray (yes/no)
- CT for pulmonary embolism (yes/no)
- Telemetry
- Cardiac arrest
- cardiogenic shock (yes/no)
- urine production

**Routine biochemistry includes: Troponin T, CKMB, NT-pro-BNP, creatinine, ferritin, neuron Specific Enolase, CRP, procalcitonin, leukocyte- and differential count, albumin, ALAT, ASAT, bilirubin, INR, creatinine, sodium, potassium, calcium, glucose, albumin, blood urea nitrogen, uric acid, red blood cell count, platelet count, HbA1c, TSH, transferrin, ferritin.

*Dead*:

- Y/N

If dead, specify presumed cause:

- Cardiovascular: progressive cardiogenic shock or fatal arrhythmia, heart failure
- Cerebral: cerebral herniation and/or severe intracranial bleeding, or withdrawal of life sustaining therapies due to brain injury
- Sepsis
- Multi Organ Dysfunction Syndrome (MODS)

*Hospital discharge*

- Time and results of MRI, CT, Echocardiography, Angiography
- PCI performed
- Number of coronary interventions
- CABG performed
- ICD inserted
- GCS at discharge
- mRS at discharge
- Length of initial hospital stay (counted from admission till discharge to home, rehabilitation facility, or death)
- LVEF at discharge/last recorded during initial hospital stay (for select centers also ECHO on day 1 and 3-5)
- Discharged to ward/home/nursing home/rehabilitation unit
- Dead before discharge

Details, if applicable:

- Echocardiography
- Pacing
- ICU
- vasopressors or inotropes
- mechanical ventilation
- renal replacement
- Chest x-ray
- CT for pulmonary embolism

#### Follow-up assessments

Follow-up assessments will occur after 30-day post-inclusion. The 30-day assessment will be done over telephone and by present visit on the hospital. The following will be recorded:

- The occurrence of any specific adverse events
- The occurrence of events defined as endpoints
- Days alive out of hospital at 30 days.
- Survival: Y/N
- Additional data capture of above listed items related to but not recorded at previous visits/initial hospital stay
- Days out of ICU and out of hospital during the first 30 days

#### Long-term follow-up

Registry based follow-up after 5 and 10 years.

- The occurrence of events defined as endpoints
- Survival: Y/N

# 13. Clinical treatment outside the treatment allocation

Besides the intervention, all patients will be treated according to current regional, national, and international guidelines at the discretion of the treating physician. Long term heart failure treatment will be planned by the treating physician according to patient preferences.

# 14. ADVERSE EVENT REPORTING

Patients in pulmonary edema are always acutely and sometimes chronic sick with a high morbidity and mortality (please see Background). Accordingly, it is difficult or impossible to assess and report all adverse events and the potential relationship with any given intervention. The overall benefit versus harm of the interventions will be assessed and reported through the primary and secondary outcomes of the trial. Accordingly, events that are frequently occurring during initial hospital-stay for these patients will therefore NOT be considered an AE in the present study include the following:

- Minor bleeding: A bleeding episode that cannot be categorized as “major” (see below) from nose, gastro-intestinal tract, oral cavity, insertion sites, intramuscular, or another site.
- Metabolic disorder: Intermittent hypo- or hyperglycemia.
- Other biochemical abnormalities: AHF-patients will frequently have highly elevated levels of acute phase reactants including CRP and fibrinogen during initial ICU stay, as well as elevated creatinine, and other biochemical markers of organ injury. Only if such is considered deviating from what can be expected in this category of patients will it be recorded as an AE/AR.

Patients will be monitored for the occurrence of an adverse event for 30 days after randomization or until hospital discharge if this occurs later than 30 days and will not be followed for adverse event reporting after this. Adverse events that in general will be potentially related to the study interventions will include death, hypotension, headache, hypo- or hyperkalemia, hyponatremia, fluid retention (peripheral edema), loss of hearing and anaphylaxis.

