In a pilot-trial by Sepehrvand et al., 25 patients with AHF were allocated to high (≥96%) and 25 patients to low (90–92%) SpO2 targets [24]. They found no differences in key primary or secondary endpoints, which the trial was underpowered for, but saw a significant prolonged hospital length-of-stay in the low target group (p=0.01) [24]. One limitation to that trial, beside the small sample size, was the time from admission to inclusion in the trial of median 11.4 (IQR 7.3, 13.5) hours.

Several therapeutic goals for patients admitted with pulmonary congestion are pertinent. Since patients suffer from severe dyspnea, a rapid relieve should be one therapeutic goal. Additionally, since a more targeted emergency treatment will potentially reduce the need for mechanical ventilation and intensive care admissions, another goal is to decrease hospital length of stay. Still, such achievements should transpire without patients experiencing organ hypoxemia or worsening heart failure in the days after the initial treatment. Adverse reactions to the treatment, such as hypoxemia or hypercapnia, should be balanced with the potential benefit in the emergency setting. Previous studies of acute heart failure have included patients up to and above 11 hours post-admission, why trial-based evidence to guide treatment in the first hours of admission is non-existing.

The effects of oxygen administration for acute heart failure in the emergency setting are still unknown and a clinical equipoise exist between restrictive or liberal oxygenation. The different strategies should be investigated in prospective trials to optimize acute treatment.

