### 14.1.1 Adverse events

An adverse event means any untoward medical occurrence in a subject to whom a medicinal product is administered, and which does not necessarily have a causal relationship with this treatment.

Adverse events (AE) will be categorized according to the definitions below. To assess specific adverse events possibly related to the trial intervention, we will collect data on the following during the first 30 days after inclusion in the trial:

- Symptomatic hypotension needing medical therapy.
- Major bleeding: Bleeding causing fatality, symptomatic intracranial bleeding.
- Renal impairment: Need for continuous renal replacement therapy or intermittent hemodialysis.
- Cardiac arrhythmias: VF, VT and AF requiring DC conversion, new need for pacing during the first 24 hours.
- Respiratory: Intubation and mechanical ventilation during admission.
- Other adverse events potentially related to the intervention with specification.

No other events will be defining as AEs.

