# Appendix 4: study-related procedures

| Time | **Screening, baseline pre-randomization assessment** | **Randomization** | **12 h post randomization** | **24 h post randomization** | **Discharge** |
| --- | --- | --- | --- | --- | --- |
| Informed consent, patient | x |  |  |  |  |
| Demographics | x |  |  |  |  |
| Inclusion/ exclusion criteria | x |  |  |  |  |
| Medical history | x |  |  |  |  |
| Concomitant medications | x |  |  | x | x |
| Routine blood test | x |  |  | x (morning) |  |
| Arterial blood gas | x |  | x | x |  |
| ECG | x |  |  | x |  |
| Vital signs | x |  | x | x |  |
| Chest x-ray | x |  |  |  |  |
| Echocardiography | x |  |  | x |  |
| Focus lung-ultrasound | X |  |  | x |  |
| ReDS | X |  |  | X |  |
| Patient-dyspnea | X |  |  | X |  |
| Plasma volume | X |  |  | X |  |
| 5Q-DL |  |  |  |  | x |
| Adverse events reporting |  |  |  |  | x |

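### The protocol's adverse-event windows do not agree, and two of them run to discharge, which may differ by arm

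*Protocol*

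**What the plan says.** Four places in the protocol set when adverse events are observed.

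- **Section 14 (Adverse event reporting):** monitoring runs "for 30 days after randomization or until hospital discharge if this occurs later than 30 days".
- **Section 14.1.1 (Adverse events):** "we will collect data on the following during the first 30 days after inclusion in the trial". No extension is mentioned. Two items in the list carry their own limit. One is "Respiratory: Intubation and mechanical ventilation during admission". The other, within the arrhythmia item, is "new need for pacing during the first 24 hours".
- **Follow-up assessments (under Data collection process):** "Follow-up assessments will occur after 30-day post-inclusion", by telephone and hospital visit. The items recorded include "The occurrence of any specific adverse events".
- **Appendix 4 (study-related procedures):** the row "Adverse events reporting" is marked only in the discharge column. The table has no day-30 column.

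On whether stay may differ by arm, section 2 (Background) reports that an earlier pilot trial of high and low SpO2 targets "saw a significant prolonged hospital length-of-stay in the low target group (p=0.01"). That trial had 25 patients per arm, and the protocol does not give the difference in days.

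**The concern.** Time to discharge is determined after randomisation and may itself respond to the oxygen target. If the period in which a harm can be counted ends at discharge, an arm with longer stays has more time in which to record that harm, even when the underlying risk is the same. The between-arm comparison then mixes risk with length of observation.

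Two rules have this form: the extension past day 30 for patients still in hospital, and the admission limit on intubation and mechanical ventilation. The second matters more. Respiratory failure is the harm of most interest when two oxygen targets are compared, and intubation or ventilation is not among the primary or secondary outcomes in section 7. If the admission limit is taken as the index stay, an intubation at a readmission within 30 days would not meet the item's definition. Readmission is a realistic event here: section 2 says that up to a third of these patients die or are re-hospitalised within 3 months.

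**Working it through.** **Plan's own figures.** The adverse-event sections state no rate, window calculation or power. The only design figure is the sample size, and it reproduces: 2 × (1.960 + 1.282)² × 6.8² / 4² = 60.7, so 61 per group and 122 in total. It does not depend on the adverse-event window.

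**The four rules applied to two hypothetical patients**

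| Place | Intubated on day 10 at a readmission | Intubated on day 33 of the index stay |
|---|---|---|
| Section 14 | inside the window | inside the window (extension) |
| Section 14.1.1 | inside the 30 days; meets the item only if a readmission counts as admission | outside the 30 days |
| 30-day contact | can be recorded | not yet occurred |
| Appendix 4, read alone | after the only mark | before the only mark |

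The rules give different answers for each patient.

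**Size of the stay-dependence.** Let L be the length of stay. The protocol gives no values, so L is assumed lognormal with median m and log-SD s. Deaths are ignored.

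- Section 14 window: E[max(30, L)] = 30 + E[(L − 30)+].
- Admission item, if it means the index stay and is capped at day 30: E[min(30, L)] = E[L] − E[(L − 30)+].
- Lognormal mean: E[L] = m·exp(s²/2).
- Excess beyond day 30: E[(L − 30)+] = E[L]·Φ((ln(m/30) + s²)/s) − 30·Φ(ln(m/30)/s).
- Constant hazard: the ratio of expected events equals the ratio of exposure times.
- Front-loaded hazard: assumed proportional to exp(−t/2), with t in days, so expected events are proportional to E[1 − exp(−L/2)], with L capped at 30.

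Worked case, medians 7 v 10 days, s = 1.0:

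- m = 7: E[L] = 7 × 1.6487 = 11.54. The excess is 11.54 × 0.3245 − 30 × 0.0728 = 1.56. The section 14 window is 31.56 days and the in-hospital window is 11.54 − 1.56 = 9.98 days.
- m = 10: E[L] = 16.49. The excess is 16.49 × 0.4607 − 30 × 0.1360 = 3.52. The two windows are 33.52 and 12.97 days.
- Ratios: 33.52/31.56 = 1.06 and 12.97/9.98 = 1.30.

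All scenarios (simulated, so the last digit can differ slightly from the formula):

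| Median stay, days (s) | In hospital after day 30 | Section 14 window, days | Ratio | In-hospital window, days | Ratio, constant hazard | Ratio, front-loaded |
|---|---|---|---|---|---|---|
| 5 v 7 (0.8) | 1.3% v 3.5% | 30.14 v 30.45 | 1.01 | 6.75 v 9.20 | 1.36 | 1.07 |
| 5 v 7 (1.0) | 3.7% v 7.3% | 30.67 v 31.56 | 1.03 | 7.57 v 9.98 | 1.32 | 1.07 |
| 7 v 10 (0.8) | 3.5% v 8.5% | 30.45 v 31.36 | 1.03 | 9.19 v 12.42 | 1.35 | 1.05 |
| 7 v 10 (1.0) | 7.3% v 13.6% | 31.56 v 33.52 | 1.06 | 9.97 v 12.97 | 1.30 | 1.05 |
| 5 v 10 (1.0), extreme | 3.7% v 13.6% | 30.67 v 33.51 | 1.09 | 7.58 v 12.98 | 1.71 | 1.12 |
| 10 v 14 (1.0), extreme | 13.6% v 22.3% | 33.53 v 37.06 | 1.11 | 12.97 v 16.06 | 1.24 | 1.03 |

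With one 30-day window for every patient, the ratio of planned observation time is 30/30 = 1.00, whatever the stay.

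**The case against.** A reader might infer that the arm staying longer is observed longer throughout and so collects more events by construction. The documents do not support that. Section 14 gives every patient at least 30 days, so patients discharged on day 5 and day 20 are followed equally long; only days in hospital beyond day 30 add time.

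Nor do they establish that a readmission intubation is lost. Section 14.1.1 does not specify the index admission, and elsewhere the protocol refers to the initial stay when it means that. The 30-day contact asks every patient about adverse events, section 14.1.2 treats an in-patient admission as serious, and section 13.6 collects hospitalisations until the study ends. Likewise, it is not certain that a day-33 intubation counts: that requires the section 14 extension to override the 30-day limit in section 14.1.1. Appendix 4 is better read as an incomplete schedule than as a rule for discharge-only collection, since it omits the day-30 assessment altogether.

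The larger ratios are upper-end illustrations. They need a constant hazard, which is doubtful in an acute condition with a 24-hour intervention. Intubation also prolongs the stay, so stay is not pure exposure time. Finally, section 14 judges benefit and harm through the primary and secondary outcomes. Of these, mortality and days alive out of hospital are fixed at day 30, and section 12 names no between-arm test of adverse events.

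All of this limits the size of the problem. It does not remove the disagreement on events after day 30, the ambiguity of the admission limit, or the missing day-30 mark. The 30-day contact does not change how the respiratory item is defined, and an analysis plan cannot recover events that sites were not clearly told to record.

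**Conclusion.** The point holds as an inconsistency with a modest potential for bias. The four places must be reconciled, and two of the rules let observation depend on discharge.

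- **Extension past day 30:** about 1–6% more observation in a longer-stay arm under plausible assumed stays, and about 10% in extreme ones. If the 30-day limit in section 14.1.1 governs, the extension has no effect on the listed events.
- **Respiratory item, only if it means the index stay:** about 1.3–1.4 times the exposure, hence expected events, under a constant hazard (1.24–1.71 including the extreme scenarios). With a front-loaded hazard the excess is about 5–7% (3–12% including the extremes).

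The lengths of stay, their spread and the hazard shapes are all assumptions. That stays differ at all rests on one small pilot trial. The consequence is confined to the safety comparison; the primary outcome and the sample size are untouched. It is worth correcting because the clearest exposure to this problem is in the respiratory harm most relevant to the trial question, and the correction is cheap.

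**What to change.** Bring sections 14 and 14.1.1, the follow-up assessments and Appendix 4 to one rule:

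1. For every listed event whose window is now tied to the stay, count from randomisation to day 30, regardless of discharge or readmission. The 24-hour window for pacing does not depend on stay and raises no such problem.
2. In the respiratory item, replace the admission limit with occurrence within 30 days of randomisation.
3. List events after day 30 in patients still in hospital separately, without comparing the arms.
4. Add a day-30 column to Appendix 4 with an adverse-event mark, to match the contact that is already scheduled.

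The cost is wording only, since no new visit is needed. The small downside is that the few events after day 30 in long stayers are reported but do not enter the comparison.

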## 14.1 Definitions

All applied definitions originate from the EU regulation on clinical trials on medicinal products for human use, and repealing Directive 2001/20/EC.

### 14.1.1 Adverse events

An adverse event means any untoward medical occurrence in a subject to whom a medicinal product is administered, and which does not necessarily have a causal relationship with this treatment.

Adverse events (AE) will be categorized according to the definitions below. To assess specific adverse events possibly related to the trial intervention, we will collect data on the following during the first 30 days after inclusion in the trial:

- Symptomatic hypotension needing medical therapy.
- Major bleeding: Bleeding causing fatality, symptomatic intracranial bleeding.
- Renal impairment: Need for continuous renal replacement therapy or intermittent hemodialysis.
- Cardiac arrhythmias: VF, VT and AF requiring DC conversion, new need for pacing during the first 24 hours.
- Respiratory: Intubation and mechanical ventilation during admission.
- Other adverse events potentially related to the intervention with specification.

No other events will be defining as AEs.

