### 14.1.2 Serious adverse events

A serious adverse event is defined by regulatory agencies as one that suggests a significant hazard or side effect, regardless of the investigator’s or sponsor’s opinion on its relationship to investigational product. This includes, but may not be limited to, any event that (at any dose):

- is fatal
- is life-threatening (places the subject at immediate risk of death)
- requires in-patient hospitalization or prolongation of existing hospitalization
- is a persistent or significant disability/incapacity
- results in a congenital anomaly or birth defect

A hospitalization meeting the regulatory requirement for “serious” criteria is any in-patient hospital admission or prolongation hereof should be considered a serious adverse event.

Any event that does not exactly meet this definition yet which, in the investigator’s opinion, represents a significant hazard can be assigned the “other significant hazard” regulatory reporting serious criteria.

Additionally, important medical events that may not be immediately life threatening or result in death or hospitalization, but which may jeopardize a subject or require intervention to prevent one of the outcomes listed above, or result in urgent investigation, may be considered serious. Examples include allergic bronchospasm, convulsions, and blood dyscrasias.

Severity of adverse events

For each AE, severity will be graded accordingly:

- Mild: Transient symptoms, no interference with patient’s daily activities.
- Moderate: Marked symptoms, moderate interference with patient’s daily activities.
- Severe: Considerable interference with patient’s daily activities.

Relationship of AE to trial intervention

For each AE, relationship to trial intervention will be rated accordingly:

- Probable: Good reason and enough documentation to assume a causal relationship.
- Possible: A causal relationship is likely and cannot be excluded.
- Unlikely: The event is most likely related to an etiology other than the intervention.
- Unknown: Causality is not assessable.

An AE with a possible or probable relationship to the trial intervention will be categorized as an adverse reaction (AR).

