## 13.5 Reporting

At each assessment of an AE/AR, it must be evaluated if it should be categorized as a serious adverse event/ (SAE), and if so, this must be reported to the trial sponsor. The trial sponsor will evaluate all SAE/SAR.

Death resulting from circulatory collapse will be recorded but will not be reported to the ethical committee outside the annual reports, as AHF patients have a ≥20% risk of death within 30 days. The death rate will have no essential information in the monitoring of trial by authorities.

All SAEs occurring at the trial centers will be submitted once a year by the sponsor and a safety report of all trial patients will be submitted to the ethical committee.

No later than 90 days after the trial has been completed, the trial sponsor will notify the ethical committee, and if the trial is stopped earlier than planned, the reasons will be reported.

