## 13.6 Reporting Procedures for All Adverse Events

All adverse events occurring after inclusion observed by the investigator or reported by the subject (whether attributed to investigational product), will be reported on the case report form. Medically significant adverse events considered related to the investigational product by the investigator or the sponsor will be followed until resolved or considered stable.

The following attributes must be assigned by the investigator: description; dates of onset and resolution; severity; assessment of relatedness to investigational product, other suspect drug, or device, and action taken. The investigator may be asked to provide follow-up information.

It will be left to an investigator’s clinical judgment as to whether an adverse event is of sufficient severity to require a subject’s removal from treatment. A subject may also withdraw voluntarily from treatment because of what he or she perceives as an intolerable adverse event. If either of these situations arises, the subject must undergo an end-of-study assessment and be given appropriate care under medical supervision until symptoms cease or the condition becomes stable. If the subject was permanently withdrawn from the study or investigational product due to a serious adverse event, this information must be included in either the initial or follow-up Serious Adverse Event Report Form or the End of Study Case Report Form. Data on deaths and hospitalizations will be collected until study termination.

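### The adverse-event definition admits unlisted events only if judged potentially related, so some events that the protocol itself defines as serious have no stated route to SAE status

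*Protocol*

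**What the plan says.** Five places in the protocol bear on this.

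- **Section 14 (opening text)** names events that will not count as adverse events because they are frequent during the initial stay. Minor bleeding is one of them, defined as any bleeding that cannot be classed as major. The monitoring window is 30 days from randomisation, or until discharge if that is later.
- **Section 14.1.1** opens with a broad definition: "An adverse event means any untoward medical occurrence in a subject to whom a medicinal product is administered", with no causal link required. It then lists five named types (hypotension, major bleeding, renal impairment, arrhythmia, respiratory) and a sixth, open item: "Other adverse events potentially related to the intervention with specification". It closes with "No other events will be defining as AEs". The bleeding item reads "Major bleeding: Bleeding causing fatality, symptomatic intracranial bleeding".
- **Section 14.1.2** defines an SAE whatever the investigator or sponsor thinks about relatedness. It covers fatal, life-threatening and disabling events, and adds that "any in-patient hospital admission or prolongation hereof should be considered a serious adverse event".
- **Section 13.5** gives the route to SAE status: "At each assessment of an AE/AR, it must be evaluated if it should be categorized as a serious adverse event". SAEs then go to the sponsor for evaluation and to the ethics committee once a year.
- **Section 13.6** says that "All adverse events occurring after inclusion observed by the investigator or reported by the subject" go on the case report form, apparently whatever the attribution. It adds that data on deaths and hospitalisations are collected until the study ends.

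**The concern.** Seriousness and relatedness are separate questions, and section 14.1.2 treats them so. Sections 14.1.1 and 13.5 together make relatedness an entry condition for every event that is not one of the five named types. Whether such an event is ever assessed for seriousness then depends on an investigator's opinion about cause, which the SAE definition expressly sets aside.

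Two sites could each follow the protocol and report differently. One that starts from section 14.1.2 would report every readmission as an SAE. One that starts from sections 14.1.1 and 13.5 would report only those it thought potentially related. The second site's SAE count would be incomplete by the protocol's own definition, and so would the yearly safety report.

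This weighs more here because section 1.5 provides for no DSMB and section 11.1 for no GCP monitoring. SAE reporting to the sponsor and the ethics committee carries much of the remaining safety oversight.

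**Working it through.** The protocol gives no figure on this point, so the check is textual: take the rules in the order a site would apply them, then trace cases through.

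**The rules**

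1. Is the event an AE? Under section 14.1.1, yes if it is one of the five named types or is judged potentially related; otherwise no. Section 14 also removes bleeding that is not major.
2. Is the AE serious? Section 13.5 asks this only of an AE or adverse reaction.
3. What is serious? Under section 14.1.2, any event meeting the listed criteria, whatever the view on relatedness.

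Step 3 covers events that step 1 has already removed, and step 2 offers no other way in.

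**Cases**

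| Event | SAE by 14.1.2? | AE by 14 and 14.1.1? | Reaches 13.5? |
|---|---|---|---|
| Symptomatic intracranial bleed | Yes | Yes, named | Yes |
| Readmission judged potentially related | Yes | Yes, sixth item | Yes |
| Readmission on day 12 judged unrelated | Yes | No | No stated route |
| Ischaemic stroke needing admission or prolonging the stay, judged unrelated | Yes | No | No stated route |
| Non-fatal gastrointestinal bleed prolonging the initial stay | Yes | No: not major, so minor and excluded | No stated route |

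The bleeding case differs from the other two. Major bleeding in section 14.1.1 is only fatal or symptomatic intracranial bleeding, so every other bleed falls into the minor class that section 14 says is not an AE. That exclusion carries no exception for events judged related, so the sixth item does not clearly rescue it.

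**Does another section repair the gap?**

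- Section 13.6 requires all AEs to be reported, but section 14.1.1 decides what an AE is. It can be read consistently with the restricted list and does not bring the missing events back.
- The opening definition in section 14.1.1 would repair it, since it needs no causal link, but the closing sentence of the same section overrides it.
- The relatedness scale in section 14.1.2 includes an unlikely rating. An unlisted event could hardly receive it if potential relatedness is its condition of entry. This suggests that the sections were not drafted to work together.

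**What is still captured elsewhere?**

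- Deaths and hospitalisations: section 13.6. Mortality and days alive out of hospital at day 30 are secondary outcomes (section 7.2), and both are recorded at the 30-day follow-up.
- ICU need, mechanical ventilation, renal replacement, cardiac arrest, cardiogenic shock and ECG signs of ischaemia: the daily inpatient data in the section on the data collection process.

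These fields preserve much of the event data. They do not give an event SAE status or send it to the sponsor and the ethics committee, and days alive out of hospital does not show why a patient was readmitted.

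**The case against.** The strongest reply has four parts.

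**A restricted list is a reasoned choice.** Section 14 explains that these patients have many events and that benefit and harm will be judged through the primary and secondary outcomes. This stands for non-serious events. It does not explain why events that section 14.1.2 calls serious should fall outside the reporting route.

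**The list is not fully closed.** The sixth item admits anything potentially related, and the possible rating in section 14.1.2 refers to causality that cannot be excluded, so a cautious investigator could admit most events. This stands: the gap is confined to events judged unrelated and to bleeding that is not major. A reader might infer that no unlisted event can ever become an SAE; the text does not support that.

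**Section 13.5 also says that all SAEs at the centres are submitted yearly,** without limiting this to listed AEs. A site could rely on that sentence together with section 14.1.2. This shows that a fuller reading is available, not that the protocol settles on it.

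**Harm is captured anyway.** A reader might infer that readmissions go unrecorded, or that a difference in serious harm between the arms could not be seen. Neither follows. Hospitalisations are collected, readmission days enter a secondary outcome, and mortality, ICU days and several organ-support measures can be compared.

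It is also tempting to add non-invasive ventilation to the missing harms, because the respiratory item reads "Respiratory: Intubation and mechanical ventilation during admission". The protocol does not say whether mechanical ventilation includes non-invasive support, and section 2 describes such support as recommended initial therapy. Whether to list it is a choice for the sponsor and no part of this contradiction.

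**Conclusion.** The point holds as a contradiction within the protocol. Sections 14, 14.1.1 and 13.5, followed as written, yield a set of SAEs that is incomplete by section 14.1.2. The events affected are unlisted serious events judged unrelated, and bleeding that is serious but neither fatal nor symptomatic intracranial. What they lose is SAE status, evaluation by the sponsor, a place in the yearly submission and, for readmissions, a reported cause. The events themselves largely remain in the trial data.

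The number affected cannot be derived from the documents. They give no 30-day readmission rate: the figure in section 2, up to a third, combines death and re-hospitalisation over 3 months. Nor do they indicate how often investigators would judge an event unrelated. The conclusion does not depend on a count. It assumes only that sites apply the closing sentence of section 14.1.1 and the first sentence of section 13.5 as they stand.

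**What to change.** Reconcile sections 14, 14.1.1, 14.1.2, 13.5 and 13.6 with three changes.

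1. In section 14.1.1, replace the closing sentence with wording to this effect: *Non-serious events are recorded only if listed above. Every event meeting section 14.1.2 from randomisation to day 30, or to discharge if later, is recorded as an SAE, whether or not it is listed or thought related.*
2. In section 13.5, require seriousness to be assessed for every untoward event, not only for one already classed as an AE or adverse reaction.
3. In section 14, state that the exclusions for frequent events, including minor bleeding, apply only when the event is not serious.

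The cost is protocol and eCRF wording and somewhat more SAE forms. Hospitalisation data and the 30-day contact are already planned, and the sponsor's aim of not recording trivial events is kept. The change affects recording and reporting only, not treatment.
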